**Table 6-1 Daratumumab Infusion Rates**

|                                         | Dilution volume | Initial rate (first hour) | Rate increment | Maximum rate |
|-----------------------------------------|------------------------|----------------------------------|-----------------------|---------------------|
| First infusion                   | 1000 mL                | 50 mL/hour                       | 50 mL/hour every hour | 200 mL/hour         |
| Second infusiona      | 500 mL                 | 50 mL/hour                       | 50 mL/hour every hour | 200 mL/hour         |
| Subsequent infusionsb | 500 mL                 | 100 mL/hour                      | 50 mL/hour every hour | 200 mL/hour         |

a Escalate only if there were no Grade 1 (mild) or greater infusion reactions during the first 3 hours of the first infusion.

b Escalate only if there were no Grade 1 (mild) or greater infusion reactions during a final infusion rate of  $\geq 100$  mL/hr in the first two infusions.

### **6.3.5 Daratumumab Administration (Subcutaneous Injection)**

Daratumumab will be administered by subcutaneous (SC) injection as a fixed-dosed of 1800 mg by manual push over 3 to 5 minutes in the abdominal SC tissues in left/right locations, alternating between individual doses. The volume of the SC solution will be 15 mL for the 1800 mg dose. The dose of daratumumab will remain constant throughout the study.

As noted in the Schedule of Events, all subjects will be observed for 1 hour after the first dose of subcutaneous daratumumab during Cycle 1 Day 1 and, if deemed necessary by the treating investigator,

after subsequent injections (all patients will be switching from the IV formulation; there will be no new starts). If a subject experiences any significant medical event, then the treating investigator should assess whether the subject should stay overnight for observation. If the subject has not experienced a significant medical event but is hospitalized overnight only for observation, then the hospitalization should not be reported as a serious adverse event. Reasons for continued observation on subsequent daratumumab injections may include but are not limited to the following: subjects with a higher risk of respiratory complications (eg, subjects with mild asthma or subjects with COPD who have an FEV1 < 80% at screening or developed FEV1 <80% during the study without any medical history), subjects with injection-related reactions (IRRs) with first injection of study drug, or subjects with a decreased condition on day of dosing compared to the prior dosing day.

Patients with a history of obstructive pulmonary disorders may require additional post-infusion medications to manage respiratory complications. Consider prescribing short- and long-acting bronchodilators and inhaled corticosteroids for patients with obstructive pulmonary disorders.

#### **6.3.5.1 Daratumumab SC Dosing**

Daratumumab SC injection will be administered as follows:

- Cycles 1-2: Days 1, 8, 15, 22
- Cycles 3-8: Days 1, 15
- Cycles 9-24: Day 1

All daratumumab administrations will be in an outpatient setting. Subjects will receive concomitant medications as outlined in [Section 6.2.2](#).

Vital signs should be monitored extensively on Cycle 1 Day 1 before, and after the first administration of daratumumab. For all other administrations, vital signs should be measured before the start of injection and at the end of the injection. If the subject experiences any significant medical event, then the investigator should assess whether the subject should stay overnight for observation. If the subject has not experienced a significant medical event but is hospitalized overnight only for observation, then the hospitalization should not be reported as an SAE.

If an infusion-related reaction (IRR) develops, then the injection should be temporarily interrupted or slowed down. In the event of a life-threatening IRR (which may include pulmonary or cardiac events) or anaphylactic reaction, dara-SC should be discontinued, and no additional dara-SC should be administered to the participant. See Section 6.5.1 for instructions on the management of IRRs.

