| Sample Size  | 
A total of 45 non-transplant candidates and/or transplant candidates who agreed to defer transplant will be enrolled.
                                                                                                                                                                                                                                                                                                                                                                                                                                                                                                                                                                                                                                                                                                                                                                                                                                                                                                                                                                                                                                                                                                                                          |
| Study Design | 
This study will be a multi-center, open-label, phase 2 study, enrolling subjects with newly diagnosed MM who require systemic chemotherapy.
 
Dose Schedule and Dose Levels
Dosing schedule is based on 28-day cycles.
 
Daratumumab
Daratumumab (1800 mg) will be administered by SC injection by manual push over approximately 3 – 5 minutes in the abdominal subcutaneous tissues in the left/right locations, alternating between individual doses. The volume of the SC solution will be 15 mL for the 1800 mg dose.
 
 
• Cycles 1-2: Days 1, 8, 15, and 22
 
• Cycles 3-8: Days 1 and 15
 
• Cycles 9-24: Day 1
 
 
Carfilzomib
 
 
- Cycle 1: Days 1 and 2: 20 mg/m^2 IV infusion
 
                                                                                                                                                                                                                                                                                                                                                                                         |

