### 6.3.4 Daratumumab IV Administration *(IV administration is discontinued and not available after the approval of version 7 of protocol dated February 20, 2023)*

Daratumumab can be administered by IV infusion or subcutaneous injection as assessed by the treating investigator. Method of daratumumab administration will be patient-specific and based on treating investigator's assessment.

Daratumumab (16 mg/kg) can be administered as an IV infusion. Each subject's dose will be calculated based on the subject's weight at Cycle 1 Day 1 rounded to the nearest kilogram. The dose of daratumumab will remain constant throughout the study, unless the subject's weight changes more than 10% from Cycle 1 Day 1. All infusions will be planned as outpatient visits. On daratumumab infusion days, subjects will receive the following medications 1 hour prior to infusion; however, premedication up to 3 hours before

the dose of daratumumab is permitted:

- oral antipyretics (acetaminophen 650 to 1000 mg)
- oral or intravenous antihistamine (diphenhydramine 25 to 50 mg or equivalent).

Daratumumab IV will be administered as follows:

- Cycle 1: 16 mg/kg weekly **OR** Cycle 1 Day 1: 8 mg/kg Day 2: 8 mg/kg, Day 8, 15, 22: 16 mg/kg
- Cycle 2: 16 mg/kg weekly
- Cycles 3-8: 16 mg/kg IV infusion every 2 weeks
- Cycles 9-24: 16 mg/kg IV infusion Day 1

The dilution volumes, initial infusion rates, and increment for the first, second, and subsequent doses are provided in Table 6-1. The first infusion, cycle 1, with a volume of 1,000 mL, takes approximately 8 hours or with a volume of 500 mL, takes approximately 4 hours; the second and subsequent infusions, with volumes of 500 mL, take approximately 4 hours. The maximum infusion rate for all infusions is 200 mL/hour for cycle 1 and any subjects experiencing a Grade 1 or greater infusion reaction. Beginning cycle 2, subjects without a Grade 1 or greater infusion reaction during cycle 1 may receive daratumumab over 90 minutes. Infuse at a rate so that 20% of the calculated dose is infused over the first 30 minutes (200 mL/hour). If tolerated, infuse the remaining 80% of the dose over 60 minutes (400 mL/hour), resulting in an estimated 90 minute infusion (total volume=500 mL). The supporting company may modify the infusion rates or the pre-infusion medications prospectively based upon the information collected to date from this and other studies.

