**Table 6-5 Daratumumab Administration Window**

| Cycles  | Frequency             | Dose Held | Dosing Re-start                        |
|---------|-----------------------|-----------|----------------------------------------|
| 1 and 2 | Weekly (q1wk)         | >3 days   | next planned weekly dosing date        |
| 3 to 6  | Biweekly (q2wks)      | >7 days   | next planned biweekly dosing date      |
| 7+      | Every 4 weeks (q4wks) | >7 days   | next planned every 4 weeks dosing date |

If a dose is delayed, then the dates of all subsequent doses must be adjusted. Any dose hold of more than 14 days due to toxicity will result in permanent discontinuation of daratumumab. Dose holds of more than 14 days for other reasons should be discussed with the Lead Principal Investigator. If a dose delay occurs, then pharmacokinetic and pharmacodynamic assessments should be performed on the actual day of study drug administration, not on the original scheduled administration day.

For infusion-related reactions of any grade/severity, immediately interrupt the daratumumab infusion and manage symptoms. Management of infusion reactions may further require reduction in the rate of infusion, or treatment discontinuation of daratumumab as outlined below:

- Grade 1-2 (mild to moderate): Once reaction symptoms resolve, resume the infusion at no more than half the rate at which the reaction occurred. If the patient does not experience any further reaction symptoms, infusion rate escalation may resume at increments and intervals as appropriate ([Table 6-1](#)).
- Grade 3 (severe): If the intensity of the reaction decreases to Grade 2 or lower, consider restarting the infusion at no more than half the rate at which the reaction occurred. If the patient does not experience additional symptoms, resume infusion rate escalation at increments and intervals as outlined in [Table 6-1](#). Repeat the procedure above in the event of recurrence of Grade 3 symptoms. Permanently discontinue daratumumab upon the third occurrence of a Grade 3 or greater infusion reaction.

- Grade 4 (life threatening): Permanently discontinue daratumumab treatment.

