31. One bone marrow sample for central Minimal Residual Disease (MRD) analysis by NGS at Adaptive Biotechnologies will be collected from all subjects: 1) screening (sample is required for calibration of MRD by gene sequencing. In the event that a superfluous bone marrow aspirate –BMA- sample from screening was not available, slides of BMA smear or clot from a time prior to enrollment can be used), 2) end of cycle 8, 3) end of cycle 24 (EOT), 4) 1 and 2 years after EOT for all subjects; 5) any time that a bone marrow is performed as SOC to assess CR response. If CR is suspected after cycle 8, the bone marrow biopsy/aspirate must be performed at the end of Cycle 12. For any bone marrow collected after Cycle 8 or Cycle 24, the visit may be done on Day 22-28 of that cycle.
32. A CT-PET will be performed to confirm MRD-negative disease per Standard of Care, at every time-point when MRD is checked (+/- 2 weeks). A bone marrow done as SOC 1 and 2 years after the EOT BM will be tested for MRD and a CT-PET done to confirm MRD-negative disease (+/- 2 weeks).
33. Local testing for hepatitis B surface antigen (HBsAg), hepatitis B surface antibody (Anti-HBs), and hepatitis B core antibody (Anti-HBc). HBV serology is not required at Screening if this was performed as part of standard of care within 3 months prior to first dose.
34. For subjects with serologic evidence of resolved HBV infection (i.e., positive Anti-HBs or positive Anti-HBc) at Screening, HBV DNA testing by PCR must be performed locally.
35. Q12W for up to 6 months after the last dose of study treatment.
36. If administered by subcutaneous (SC) injection, daratumumab will be provided as a fixed-dose of 1800 mg and 30,000 units hyaluronidase per 15 mL (120 mg and 2,000 units/mL) for all cycles. All subjects receiving daratumumab subcutaneous injection will be observed for at least 6 hours after the end of the SC injection during Cycle 1 Day 1 and, if deemed necessary by the treating investigator, after subsequent injections.
37. No provider patient visits will be held on Cycle 1, Day 22.

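### Daratumumab in Cycles 1-2: the dosing text gives Days 1, 8, 15 and 22 (8 doses), the Appendix 8 grid leaves Day 22 blank (6 doses), and one row of Table 6-5 does not match the schedule for Cycles 7-8

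*Protocol*

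**What the plan says.** **Cycles 1-2, dosing text.** The synopsis (Study Design) gives "Cycles 1-2: Days 1, 8, 15, and 22", and Section 6.3.5.1 gives "Cycles 1-2: Days 1, 8, 15, 22". Table 6-5 lists Cycles 1 and 2 as weekly. The discontinued IV route in Section 6.3.4 was also weekly ("Cycle 2: 16 mg/kg weekly"), and its split-first-dose option for Cycle 1 names Day 22.

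**Cycles 1-2, grid.** In the Appendix 8 table for induction Cycles 1-4, the daratumumab row has an entry on Day 1, a Cycles 1-2 label on Day 8 and an entry on Day 15. Day 22 is empty. Vital signs are also empty on Day 22. Section 6.3.5.1, after a stricter rule for Cycle 1 Day 1, says that for all other administrations "vital signs should be measured before the start of injection and at the end of the injection". The last footnote to Appendix 8 adds: "No provider patient visits will be held on Cycle 1, Day 22".

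**Cycles 7-8.** The synopsis, Section 6.3.5.1 and the consolidation grid give Days 1 and 15 through Cycle 8. Table 6-5 puts Cycles 3 to 6 on a two-weekly footing and labels Cycle 7 onward "Every 4 weeks (q4wks".

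**Who is affected.** Section 6.3.5 says of the subcutaneous route that "all patients will be switching from the IV formulation; there will be no new starts".

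**The concern.** Daratumumab is the drug this trial adds to KRd, and the primary endpoint (sCR and MRD negativity) is read at the end of Cycle 8. A site working from the grid and a site working from Section 6.3.5.1 would plan different exposure in the loading cycles behind that endpoint.

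The conflict also reaches monitoring and a second drug. If Day 22 is an injection day, the grid does not carry the vital signs that Section 6.3.5.1 requires. Section 6.3.3 splits the dexamethasone dose in weeks with a daratumumab injection, so the status of Day 22 also decides whether that week's dexamethasone is split.

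The row for Cycle 7 onward in Table 6-5 is a separate matter. It determines when dosing resumes after a held dose, and it assumes an interval that the rest of the protocol does not use until Cycle 9.

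**Working it through.** The protocol states no total number of daratumumab doses, so there is no figure to reproduce. The check is a reading of the grid followed by a dose count.

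**Step 1. Is the blank cell real?** The tables were read by machine, so alignment matters. The day header of the induction table and the daratumumab row each have 10 cells. Matched cell by cell, the row reads Day 1 marked, Day 2 blank, Day 8 labelled Cycles 1-2, Day 9 blank, Day 15 marked, Day 16 blank, Day 22 blank. The dexamethasone row, also 10 cells, keeps its Day 22 entry, and so does the pregnancy test row. The column is in use, and the empty Day 22 vital signs agree with the blank. A lost entry cannot be fully excluded but is unlikely.

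**Step 2. Doses by source.** Inputs are the days per cycle in each source and, for later cycles, the schedule on which text and grid agree: Days 1 and 15 in Cycles 3-8, Day 1 in Cycles 9-24.

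| Span | Text | Appendix 8 grid |
|---|---|---|
| Cycles 1-2 | 2 × 4 = 8 | 2 × 3 = 6 |
| Cycles 3-8 | 6 × 2 = 12 | 6 × 2 = 12 |
| Through Cycle 8 | 8 + 12 = 20 | 6 + 12 = 18 |
| Cycles 9-24 | 16 × 1 = 16 | 16 × 1 = 16 |
| Through Cycle 24 | 20 + 16 = 36 | 18 + 16 = 34 |

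The difference is 2 doses: 2/8 = 25% of the Cycles 1-2 total and 2/20 = 10% of the total through Cycle 8. At the fixed 1800 mg dose, Cycles 1-2 come to 8 × 1800 = 14,400 mg or 6 × 1800 = 10,800 mg.

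**Step 3. Does the route matter?** No. Section 6.3.4 is weekly for IV in Cycles 1 and 2 (the Day 1/Day 2 split in Cycle 1 divides one dose), so the grid conflicts with either route.

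**Step 4. Restart dates in Cycles 7-8.** Table 6-5 sends a missed dose to the next planned date at the row's frequency. Counted from the held dose, a two-weekly calendar resumes 14 days later and a four-weekly calendar 28 days later. If the four-weekly calendar is instead anchored on Day 1, a missed Day 15 dose resumes on Day 1 of the next cycle either way. The table does not say which count applies. Section 6.5.1.1 has a separate rule that a delayed Day 1 moves the whole cycle.

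**The case against.** **The dosing instructions agree with each other.** For Cycles 1-2, the synopsis, Section 6.3.5.1, Table 6-5 and the old IV text all say weekly. Section 6 introduces the calendar as an overview, and the grid is loose elsewhere: it marks lenalidomide on Day 22 in Cycles 9-24, although Section 6.3.2 forbids it past Day 21. This lowers the chance that a site would drop the dose. It does not remove the contradiction in the table that sites use to book visits.

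**The forward effect may be small.** If there are no new starts, few or no patients would receive subcutaneous loading doses under this version. That stands. The conflict could still have applied to earlier IV patients, but nothing in the protocol shows that any site followed the blank cell.

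**Stronger readings that a reader might infer, and that the documents do not support:**

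- *The last footnote cancels the Day 22 dose.* It concerns a provider visit, in Cycle 1 only, and does not mention dosing. An injection without a provider visit is compatible with it. The 6-dose count rests on the blank cell alone.
- *Table 6-5 is a competing regimen, giving still lower totals through Cycle 8.* It governs administration windows and restarts. The regimen for Cycles 7-8 is stated consistently in the synopsis, Section 6.3.5.1 and the grid.
- *The grid must carry Day 22 hematology because of the hold rule.* Section 6.1.2 and the grid agree on blood counts on Days 1, 8 and 15, before carfilzomib, and the hold criteria in Section 6.5.1.1 do not ask for a same-day count. Requiring one would be a new monitoring rule. It is fair only to ask that these passages be made consistent.
- *The primary test is compromised.* No effect of 2 doses on the response rate or on the binomial test is shown.

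**Conclusion.** The contradiction holds. The dosing text gives 8 daratumumab doses in Cycles 1-2 and 20 through Cycle 8; the Appendix 8 grid gives 6 and 18. The grid also lacks the Day 22 vital signs that Section 6.3.5.1 would require if Day 22 is an injection day. Separately, the Table 6-5 row for Cycle 7 onward does not match the Days 1 and 15 schedule through Cycle 8 and leaves the restart date after a held dose open to two readings.

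This rests on the blank Day 22 cell being as printed, which the cell count and the neighbouring rows support. The consequence is inconsistent operating instructions for the drug under test and unclear planned exposure behind the primary endpoint. It is not a demonstrated error in the primary analysis. The documents do not settle which schedule is right.

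**What to change.** 1. Reconcile the synopsis, Sections 6.3.4 and 6.3.5.1, Table 6-5, the Appendix 8 daratumumab row and the last Appendix 8 footnote, so that one daratumumab schedule is stated for Cycles 1-2 and one for Cycles 7-8. The footnote should say whether it bears on dosing.
2. Reconcile the grid's Day 22 assessments with that schedule, with the vital-sign requirement in Section 6.3.5.1 and with the hold criteria in Section 6.5.1.1.
3. Tabulate the daratumumab doses actually given through Cycle 8, by cycle, beside the primary result, so that the reader can see the exposure patients had. If the SAP, which is not at hand, already plans such a table, a cross-reference is enough.

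The cost is a protocol clarification, a corrected grid and one exposure table from dosing data that the case report forms already collect.

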#### **6.4 Instructions for Initiation of a New Cycle**

A new course of treatment may begin on the scheduled Day 1 of a new cycle if all of the following are met:

- $ANC \geq 1.0 \times 10^9/L$
- Platelet count  $\geq 30 \times 10^9/L$
- Any other study drug-related adverse event must have resolved to Grade 1 or baseline (see Appendix 2)
- Serum uric acid and creatinine concentrations must return to baseline prior to carfilzomib doses during Cycles 1 and 2

If  $ANC < 1.0 \times 10^9/L$  but  $> 0.75 \times 10^9/L$ , the start of a new cycle is at the discretion of the treating investigator

If these conditions are not met on Day 1 of a new cycle, the subject will be evaluated weekly, and a new treatment cycle will not be initiated until the toxicity has resolved, as described above.

If daratumumab, carfilzomib, or lenalidomide, or daratumumab are held for the remainder of the previous cycle or the new cycle is delayed due to residual toxicity on the planned Day 1 of the next cycle, then the new cycle will be started at 1 dose decrement.

If a delay of starting a new cycle is greater than 21 days, the subject should be discontinued from treatment, unless continuing treatment is mutually agreed upon by the site Lead Principal Investigator at the University of Chicago and the co-investigator at the treating institution.

Dexamethasone may be discontinued without the subject discontinuing study treatment.

